### Interventions

PTSD Coach was developed by the VA’s National Center for PTSD Dissemination and Training Division as a self-managed mobile app that contains 4 sections: learn, self-assessment, manage symptoms, and find support [34]. The app is available at no cost from the App Store and Google Play marketplaces [35] and thus reaches almost all (99.5%) US smartphone users [36]. For this research project, the app is available in both English and Spanish. The primary focus of PTSD Coach is on PTSD symptoms, which include (1) reexperiencing, such as having intrusive traumatic symptoms (eg, flashbacks and nightmares); (2) persistent avoidance of stimuli associated with the traumatic event; (3) negative thoughts or feelings that worsened after the traumatic event; and (4) hyperarousal, such as sleep disturbance, excessive startle reactions, and irritable behavior [37]. PTSD Coach provides psychoeducation on trauma and PTSD and helps trauma-exposed individuals to monitor and manage traumatic stress symptoms. PTSD often cooccurs with depression and anxiety, and PTSD Coach is also effective on these symptoms [38], but it was never studied with GRs. Sleep disturbance is a common complaint among WTC responders [5], and veterans have reported that the mobile app has helped them with sleep problems [34]. In summary, the PTSD Coach app focuses on targeting the primary mechanisms of PTSD and associated symptoms of depression, anxiety, and sleep disturbance.

CS PTSD Coach was developed as a brief intervention for veteran primary care patients with elevated PTSD symptoms who were unlikely to use a mobile app on their own [34,39]. CS PTSD Coach is a manualized intervention that combines the PTSD Coach mobile app with four 20-to-30-minute sessions delivered over 8 weeks. Sessions focus on instructions for app use, setting symptom reduction goals, and assigning PTSD Coach activities (ie, symptom monitoring, management strategies, and psychoeducational readings) for completion between sessions. The clinician sessions help participants select the management strategies within the app that can best address their PTSD symptoms and incorporate these strategies into their daily lives. As part of aim 4, the existing treatment manual developed for veterans will be adapted for the GRs, including translating it into Spanish. The main components of each session are shown in Table 1.

**Table 1. T1:** Clinician-Supported PTSD Coach overview and fidelity elements.

	Session 1	Sessions 2 and 3	Session 4
Format	Audio or audio and video	Audio or audio and video	Audio or audio and video
Content	Overview of treatment Instructions for app use Discuss learn modules Complete PCL-5^a^ in app Target problem domain Try 1-2 manage strategies	Review homework Discuss change on PCL-5 graph Discuss manage strategies used Target new symptom domain to manage Problem solve any adherence issues	Review homework Discuss Learn, assessment, and manage tools used since last session Recommend treatment based on PCL-5 score Make treatment or self-management plan
Homework	Complete PCL-5 weekly Read at least 2 Learn topics Use manage strategies daily	Complete PCL-5 weekly Read at least 2 Learn topics Use manage strategies daily	Follow through on treatment plan Continue to use app as desired

a PCL-5: PTSD Checklist for DSM-5.

CS PTSD Coach is delivered by bilingual or bicultural master’s or doctoral students in social work with experience in providing remotely delivered psychosocial care, supervised by a Florida-licensed clinician. The university is a Hispanic-serving institution; most students are bilingual or bicultural Hispanics. The intervention developer leads clinician training that includes didactic training and role plays. During treatment delivery, clinicians participate in weekly group consultation calls with the intervention developer’s team. The clinicians complete fidelity checklists of essential protocol components following each session. An independent fidelity assessment will be conducted using audio-recorded sessions for 25% of sessions randomly selected from each of the 4 sessions of the protocol.

The SM PTSD intervention includes 1 brief session with the clinician who provides basic information about downloading and using the app [27]. There are no further instructions with the participants in this group.

### Measures

#### Overview

The project includes measures to assess clinical outcomes and exploratory implementation (process) outcomes, including satisfaction, feasibility, and acceptability. All outcome measures are administered by research assistant assessors who are blind to conditions and not involved in treatment delivery. The clinical measures are brief, have good psychometrics, and have been used in clinical trials, so they are sensitive to treatment change (when needed, Spanish versions of the measures will be used). Some of the instruments have been used in the WTCHP monitoring program, so would be familiar to respondents. To promote retention and completion of follow-up assessments, participants are contacted using multiple methods and reminded of upcoming assessments, and outcome data are collected remotely to minimize participant burden.

#### Clinical Outcomes

The primary clinical outcome variable, PTSD symptoms, is assessed at all 3 time points (baseline, postintervention, follow-up) using the PCL-5, which has good reliability and validity [7,40]. The PCL-5 is used to assess changes in treatment response, with items rated on a 0 (not at all) to 4 (extremely) scale and higher total scores reflecting greater PTSD symptom severity. Studies of expected minimal important difference with the PCL-5 indicated that changes under 5 are unreliable and 9 to 12 points reflect real change [41]. Thus, we expect at least a 5-point difference to be reliable change and 9 to reflect clinically meaningful differences. As few PTSD Coach studies have explored changes in specific PTSD symptom clusters [38], we will conduct exploratory subscale analyses to identify which clusters respond best to the intervention.

Depression severity, a secondary clinical outcome, is assessed at all 3 time points using the Patient Health Questionnaire-9 (PHQ-9), a reliable and valid measure [42,43] used in similar studies [28,44]. The PHQ-9 is a 9-item self-report measure of depression symptoms in the past 2 weeks. Participants rate each item on a 0 (not at all) to 3 (nearly every day) scale. A score of 5 indicates mild depression, 10 to 14 moderate, 15 to 19 moderately severe, and 20 to 27 severe [43]. Scores ranging from 8 to 11 suggest major depressive disorder [45].

Anxiety, a secondary clinical outcome, often cooccurs with PTSD [37] and is assessed at the 3 time points using the Generalized Anxiety Disorder-7 (GAD-7)[46], a 7-item self-report measure of general anxiety symptoms over the past 2 weeks. Respondents rate their anxiety on a scale from 0 (not at all) to 3 (nearly every day). The measure has good reliability and validity [46,47] and has been used with first responders [44]. A score of 8 or higher indicates probable generalized anxiety disorder [48,49], with cut points of 5, 10, and 15 indicating mild, moderate, and severe levels of anxiety, respectively [46].

Sleep disturbance symptoms, a secondary clinical outcome, is assessed using the 7-item self-report Insomnia Severity Index (ISI) [50,51]. The ISI assesses the severity and effects of insomnia symptoms over the past 2 weeks. Items are rated on a scale from 0 (no problem) to 4 (very severe problem), yielding a range of 0 to 28, with higher scores reflecting increased severity of insomnia symptoms. Scores of 0 to 7 indicate absence of insomnia, 8 to 14 subthreshold insomnia, 15 to 21 moderate insomnia, and 22 to 28 severe insomnia [50]. For clinical trials, a cut score of 11 is recommended [51], with a score of 15 indicating clinically significant insomnia symptoms [50]. A reduction of >7 points indicates optimal change for moderate improvement and a reduction of >8 points indicates optimal change for marked improvement [51].

#### Satisfaction, Feasibility, and Acceptability

In addition, several exploratory implementation (process) outcomes are intended to capture intervention uptake, user experience, and implementation potential rather than clinical efficacy. Satisfaction with treatment is assessed using the Client Satisfaction Questionnaire, a widely used 8-item self-report measure assessing patient satisfaction with care [52,53]. Each question is rated on a scale from 1 to 4, with higher scores reflecting increased satisfaction.

To assess feasibility, responder engagement with the app will be evaluated using objective use data from the app developer (VA Palo Alto Health Care System), including frequency and duration of use, peak use periods, and module-level engagement.

Treatment acceptability and appropriateness is assessed with the Acceptability of Intervention Measure and Intervention Appropriateness Measure, both consisting of 4 items with good reliability and validity [54]. Each item is rated on a scale from 1 (completely disagree) to 5 (completely agree), with higher scores indicating more acceptability and appropriateness.

To assess usability of CS PTSD Coach and the mobile app itself (depending on intervention group), we use the System Usability Scale [55] that consists of 10 items rating users’ perceived usability of a system, which has strong reliability and validity [55]. Higher scores indicate greater usability. We expect “good” usability, defined as a score of >68 [55].

### Data Collection and Management

Data are captured and managed using a secure Research Electronic Data Capture database (REDCap; Vanderbilt University) [56], created and maintained at the statistical consulting center of the host university, Florida International University. The database includes value, range, and logic checks, and undergoes 2 levels of internal system testing and revision to ensure data integrity. Data collection follows the schedule outlined earlier, which includes baseline sociodemographic information; mental health assessments (PTSD, depression, anxiety, and sleep disturbance); and postintervention evaluations of satisfaction, feasibility, and acceptability. University-based assessors enter data directly into REDCap, linked to unique IDs. Access to participant identifiers is restricted to the study coordinator and data entry team, and REDCap’s built-in quality checks help detect inappropriate values.

All data are securely stored in the Amazon Web Services cloud with encryption both in transit and at rest. The REDCap environment is protected by virtual firewalls and requires 2-factor authentication for access. App usage data collected by the VA will be identified solely by randomly generated invitation codes, ensuring full de-identification. The host university will maintain a secure linkage file connecting app use data with participant identifiers. Upon completion of data collection, deidentified data will be exported for analysis. Long-term data access and archival will follow the host university’s Division of Information Technology Security Office policies, ensuring compliance with health information privacy standards.

### Statistical Analysis Plan

In aim 1 (feasibility), we will assess the feasibility of PTSD Coach with multiethnic GRs in Florida. App use data obtained from the VA will be summarized descriptively with mean (SD) for continuous variables (eg, time spent in the app) and frequency (N) and percent (%) for categorical variables (eg, modules completed). The use patterns will be examined by the intervention group (CS vs SM) and language (English vs Spanish) used.

In aim 2 (acceptability), we will evaluate the acceptability of the CS PTSD Coach intervention. Satisfaction is assessed using the Client Satisfaction Questionnaire, with ratings of “good” or “excellent” indicating endorsement. Acceptability and appropriateness are measured using the Acceptability of Intervention Measure and the Intervention Appropriateness Measure, with agreement ratings serving as indicators of positive reception. Data will be summarized with mean (SD) for continuous variables and frequency and percent for categorical variables. The data will be summarized for the entire cohort and by both intervention and language groups.

In aim 3 (efficacy), we will evaluate the efficacy of CS PTSD Coach in reducing symptoms of PTSD, depression, anxiety, and sleep disturbance when compared with SM PTSD Coach and the waitlist control group. Changes in symptoms are measured using the PCL-5 for PTSD, PHQ-9 for depression, GAD-7 for anxiety, and ISI for sleep disturbance. Exploratory analyses will assess the responsiveness of specific PTSD symptom clusters to the 2 interventions [38]. Within-group changes will be summarized descriptively (mean change and 95% CIs) to aid interpretation.

The primary analysis will compare postintervention (8 weeks) outcomes between intervention groups using ANCOVA, adjusting for baseline outcome values and prespecified covariates (eg, language group). The primary estimand is the between-group difference in change from baseline to 8 weeks.

Separate ANCOVA models will be done to compare between-group changes from baseline to 12-week follow-up (secondary analysis) and from postintervention to 12-week follow-up (exploratory analysis). The sample size and power calculations are applicable to all ANCOVA models.

All analyses will follow an intent-to-treat framework, with missing outcome data addressed through multiple imputation and sensitivity analysis. Exploratory moderation analyses will be conducted by including prespecified interaction terms in ANCOVA models. Exploratory mediation analyses will be conducted using established regression-based approaches.

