### Aims of the Study

The overarching goal of the study is to assess the feasibility, acceptability, and efficacy of Clinician-Supported (CS) PTSD Coach, originally developed for English-speaking military veterans [27,28] but never tested with WTCHP members, for reducing symptoms of PTSD, depression, anxiety, and sleep disturbance among multiethnic English-speaking and Spanish-speaking GRs in Florida. The four primary aims are to (1) assess the feasibility of CS PTSD Coach with GRs living in Florida; (2) evaluate the acceptability of CS PTSD Coach; (3) determine the efficacy of CS PTSD Coach in reducing PTSD, depression, anxiety, and sleep symptoms through a controlled trial; and (4) develop and deliver a Spanish-language version of CS PTSD Coach.

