## Discussion

This protocol describes an RCT designed to evaluate the feasibility, acceptability, and efficacy of CS and SM versions of PTSD Coach among WTC GRs residing in Florida. Persistent mental health symptoms, combined with documented barriers to specialty care and geographic dispersion, underscore the need for scalable, accessible interventions tailored to this aging and increasingly mobile population.

The study addresses several critical gaps in the literature. Although PTSD Coach has demonstrated promise among military veteran populations, it has not previously been evaluated with WTC GRs, nor adapted for Spanish-speaking responders. By examining both CS and SM delivery models within a single trial, this study will generate comparative data on the role of human support in enhancing engagement and clinical benefit from digital mental health tools. The inclusion of bilingual delivery further advances equity by addressing linguistic barriers that contribute to unmet mental health needs among Spanish-speaking Hispanic responders.

Key strengths of the study include its randomized controlled design, use of validated outcome measures aligned with the WTCHP monitoring system, and integration of feasibility and acceptability outcomes alongside symptom change. Embedding the intervention within the context of the WTCHP and the National Provider Network enhances clinical relevance and positions the findings to inform real-world implementation should the intervention prove effective.

Several anticipated limitations warrant consideration. Recruitment may be challenged by responder aging, comorbid medical conditions, and variability in comfort with mobile technology. Attrition is a known risk in app-based interventions and may differentially affect study arms. In addition, findings may not generalize to responders living outside Florida or to those without access to smartphones or stable internet connectivity. These factors will be carefully monitored and reported to inform interpretation of study outcomes.

If successful, this trial has the potential to inform scalable mental health service delivery models for WTC responders and other disaster-exposed populations facing similar access barriers. Results will guide future effectiveness and implementation studies and may support broader integration of clinician-supported digital interventions within occupational health and disaster response systems.

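### Aim 1 names mean (SD) as the only summary for time in the app; if use is strongly skewed, the mean could overstate typical engagement, so median (IQR) and the share of non-users should be added.

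*Protocol article*

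**What the plan says.** The Aims of the Study section lists as its first primary aim to "assess the feasibility of CS PTSD Coach with GRs living in Florida". The Satisfaction, Feasibility, and Acceptability section bases feasibility on objective logs covering "frequency and duration of use, peak use periods, and module-level engagement". It introduces the measures under that heading by saying that "several exploratory implementation (process) outcomes are intended to capture intervention uptake".

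The Statistical Analysis Plan section then fixes the summaries for aim 1. For continuous data: "App use data obtained from the VA will be summarized descriptively with mean (SD) for continuous variables (eg, time spent in the app". For categorical data: "frequency (N) and percent (%) for categorical variables (eg, modules completed". On subgroups: "The use patterns will be examined by the intervention group (CS vs SM) and language (English vs Spanish) used".

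No median, quartile or range is named. No feasibility cut-off is stated, and no test of use between groups is planned.

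**The concern.** With no cut-off, the descriptive figures themselves carry the feasibility conclusion. Mean (SD) is a stated choice, not a silence that a fuller plan would fill, and it is a weak one for a variable with a floor at zero and no upper limit. If many participants use the app little and a few use it heavily, most of an arm lies below its mean, and a reader would take away more engagement than the typical participant showed. Neither the median nor the share who never opened the app can be recovered from a mean and an SD.

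Whether use will look like that is an inference. The document offers only indirect hints. CS PTSD Coach was developed for veterans in primary care with "elevated PTSD symptoms who were unlikely to use a mobile app on their own", and the Discussion mentions "variability in comfort with mobile technology".

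**Working it through.** **Plan's own figure.** There is none to reproduce. The document gives no expected time in the app, no SD and no share of non-users.

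**Inputs.**
- Arm size (Sample Size Calculation section): 40 per arm; with 10% attrition, 40 × 0.90 = 36.
- Distribution of time in the app: not given. Assumed log-normal with log-SD s from 0.3 (mild skew) to 1.5 (strong skew), with 0% or 20% non-users.

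**Closed form, no non-users.**
- Mean/median = exp(s²/2). At s = 0.3, exp(0.045) = 1.05; at 0.75, exp(0.281) = 1.32; at 1.0, exp(0.5) = 1.65; at 1.5, exp(1.125) = 3.08.
- SD/mean = √(exp(s²) − 1). At s = 1.0 this is 1.31; at 1.5 it is 2.91.

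**Simulation, 20,000 replicates, 36 per arm.** The sample mean/median ratio runs slightly below the closed form because small arms often miss the extreme tail.

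| s | Non-users | Mean/median | Share below the mean | Time held by top 4 of 36 |
|---|---|---|---|---|
| 0.3 | 0% | 1.04 | 56% | 18% |
| 0.75 | 0% | 1.30 | 64% | 31% |
| 1.0 | 0% | 1.58 | 68% | 39% |
| 1.5 | 0% | 2.70 | 75% | 55% |
| 0.3 | 20% | 0.92 | 43% | 21% |
| 1.0 | 20% | 1.74 | 68% | 44% |
| 1.5 | 20% | 3.47 | 76% | 60% |

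With equal use, the top 4 would hold 4/36 = 11%. Results at 40 per arm are nearly the same (mean/median 1.59 at s = 1.0 and 2.74 at s = 1.5, no non-users).

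The row with s = 0.3 and 20% non-users matters: there the mean lies 8% below the median. Non-users alone do not make the mean overstate use, and neither statistic reveals them. That is why their share has to be reported separately.

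**Would medians help compare CS with SM?** This was checked separately, again at 36 per arm.
- Two identical arms differ 1.5-fold or more in 17% of trials by means and 16% by medians at s = 1.0, and in 45% and 35% at s = 1.5.
- If CS use is truly 1.5 times SM use, the arms come out in the wrong order in 8.3% (means) and 7.8% (medians) at s = 1.0, and in 22.6% and 17.6% at s = 1.5.
- With 20% non-users at s = 1.0 the median does worse: 15.1% against 12.5% for the mean.

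Most of this instability is sampling noise from small arms. The median gains clearly only at the extreme of the assumed range.

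**The case against.** The strongest case against is that nothing here is an error. Adding a median is a reporting preference, and the article does not forbid it. Much of this stands.

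- **Expected skew.** A reader might infer that the document itself expects uneven use. It does not say so. The sentence about patients unlikely to use an app describes the veterans for whom CS was first built, and the remark on comfort with technology is given as a recruitment difficulty.
- **Heavy users deciding feasibility.** A reader might also infer that a few heavy users would determine the feasibility result and the arm comparison. The document does not support this. Time in the app is one example among several use measures. Counts and percentages for modules are planned too, and heavy users' minutes do not distort those. No threshold or test depends on mean minutes, and the process measures are labelled exploratory. The simulation shows little or no gain from medians in ordering the arms.
- **Mild skew.** At log-SD 0.3 the mean and median differ by about 4% to 5%, which would be immaterial.
- **The SD as a warning.** An SD larger than the mean would alert a careful reader to skew. It would not tell that reader the median or how many participants never used the app.

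What the objection does not remove is that, for a primary aim, the one continuous summary named may describe few of the participants.

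**Conclusion.** The point holds as a minor one, limited to describing the typical user. If time in the app is strongly right-skewed (log-SD 1.0 to 1.5 under a log-normal assumption), the population mean is 1.65 to 3.1 times the median, and 68% to 75% of participants in an arm of 36 fall below the arm mean. If skew is mild, the difference is about 5%. The size rests entirely on that assumed distribution, because the document supplies none. No test, sample size, decision rule or efficacy conclusion is affected, and no improvement in the CS versus SM or English versus Spanish comparison is claimed.

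**What to change.** Change the aim 1 sentence in the Statistical Analysis Plan section along these lines: *Time in the app and frequency of use will be summarized by median (IQR), with mean (SD) as an additional line, by intervention group and language; the number and percentage of participants with no or minimal recorded use will also be given.* The team should define minimal use before looking at the logs.

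The cost is one sentence and a slightly longer table. The same logs are used and no data are added. The Results section reports 63 participants enrolled as of April 2026, with analysis to begin only after follow-up is complete, so the wording can still be settled before analysis.

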### Sample Size Calculation

The rationale for selecting a sample size of 120 participants, 40 per group across the 3 arms of the RCT (CS PTSD Coach, SM PTSD Coach, and waitlist control), is based on achieving sufficient statistical power to detect meaningful differences in the outcomes. As the primary analysis is to compare the preintervention (baseline) and postintervention (8 weeks) change in outcomes across intervention arms, analysis of covariance (ANCOVA) serves as the primary between-group analytic approach as it is the most powerful model for pre- and postanalysis. Specifically, with 10% expected data attrition, this sample size will provide 80% power to detect a minimal difference of 0.30 SDs between-group means using ANCOVA with a significance level of *P*<.05. The design assumes a common within-group SD of 1.00 and covariates with an R-squared of 0.20, ensuring robust comparisons across interventions while accounting for potential confounding variables.

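### The power calculation is said to cover every ANCOVA model, but the exploratory interaction models have about 7% to 11% power at 0.30 SD

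*Protocol article*

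**What the plan says.** All references are to the protocol article.

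- **Sample Size Calculation** ties the calculation to a single analysis: "the primary analysis is to compare the preintervention (baseline) and postintervention (8 weeks) change in outcomes across intervention arms". The design is "120 participants, 40 per group across the 3 arms of the RCT". The claim is that, "with 10% expected data attrition, this sample size will provide 80% power to detect a minimal difference of 0.30 SDs between-group means using ANCOVA", at a significance level of 0.05. The variance inputs are: "The design assumes a common within-group SD of 1.00 and covariates with an R-squared of 0.20".
- **Statistical Analysis Plan** names the 8-week ANCOVA as primary. It adds separate ANCOVA models for change from baseline to 12 weeks (secondary) and from 8 to 12 weeks (exploratory), and closes that paragraph with: "The sample size and power calculations are applicable to all ANCOVA models".
- **The next paragraph of that section** says: "Exploratory moderation analyses will be conducted by including prespecified interaction terms in ANCOVA models".
- **Hypotheses and Exploratory Analyses** lists the potential moderators and mediators as baseline PTSD severity, sex, race, ethnicity, language and engagement level, and calls these analyses exploratory.

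No separate power, effect size, SD or R-squared is given for the interaction models, for 12 weeks or for the 8-to-12-week interval. The 10% attrition has no time point attached.

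**The concern.** A power calculation for a difference between two arm means does not describe a difference between two such differences. An arm-by-moderator interaction contrast has at least four times the variance of the main-effect contrast, and more when the moderator splits unevenly. Saying that the calculation applies to all ANCOVA models therefore credits the interaction tests with a sensitivity that the design cannot give them.

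At stake is how a null moderation result is read. Language is a listed moderator, and the trial delivers the intervention in two languages. A reader who trusts the sentence could take a non-significant language or sex interaction as adequately powered evidence of a similar effect in both subgroups. The data could not support that conclusion.

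**Working it through.** **Inputs**

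- From Sample Size Calculation: 40 per arm, 10% attrition, SD 1.00, R-squared 0.20, alpha 0.05. So n = 40 × 0.90 = 36 evaluable per arm, and residual variance = 1.00 × (1 − 0.20) = 0.80.
- Sidedness is not stated. Two-sided is assumed.
- Moderator splits in the trial are not given. A range of 10% to 50% for the smaller group is assumed. Two points come from the Florida cohort described under Growing WTC Subcohort in Florida: 81.6% male leaves 18.4%, and 25.9% are Hispanic. The Hispanic share is only a proxy for language, since Spanish-language participants may be fewer.

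**Step 1. The plan's own figure**

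Pairwise main effect: SE = sqrt(0.80 × 2/36) = 0.211. For 0.30 SD, 0.30/0.211 = 1.42, and Φ(1.42 − 1.96) gives 29.6% power. The difference detectable with 80% power is 2.80 × 0.211 = 0.59 SD. The stated 80% is not reproduced.

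If 0.30 is instead read as the SD of the three arm means (Cohen's f), the 2-df F test has 87.8% power with R-squared 0.20 and 79.1% with R-squared 0. So 80% appears, approximately, only when 0.30 is read as f and the stated R-squared is ignored.

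**Step 2. Interaction contrast between two arms**

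With p the smaller group's share, SE = sqrt(0.80 × (2/36) × (1/p + 1/(1 − p))). Power at 0.30 SD is Φ(0.30/SE − 1.96) + Φ(−0.30/SE − 1.96). The 80% detectable interaction is 2.80 × SE.

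| Smaller group | 1/p + 1/(1−p) | SE | Power at 0.30 SD | Detectable with 80% power |
|---|---|---|---|---|
| 50% | 4.00 | 0.422 | 11.0% | 1.18 SD |
| 25.9% (Hispanic share) | 5.21 | 0.481 | 9.6% | 1.35 SD |
| 18.4% (non-male share) | 6.66 | 0.544 | 8.5% | 1.52 SD |
| 10% | 11.11 | 0.703 | 7.1% | 1.97 SD |

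A 2-df test of interaction across all three arms, with a largest difference of 0.30 SD, gives 7% to 10% for splits from 18.4% to 50%.

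**Step 3. Sensitivity**

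- With no attrition (40 per arm) and R-squared 0.20, power is 11.7% at 50:50 and 7.3% at 10%.
- With R-squared 0.50 and 36 per arm, it is 14.7% and 8.4%.
- Under the f-type reading, with the arm-specific subgroup differences having an SD of 0.30, the 2-df interaction test has 31.7% power at 50:50, 25.1% at 25.9% and 20.4% at 18.4%. The matching main-effect figure is 87.8%.

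**Step 4. The other two models**

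- *12 weeks.* The arms and the type of contrast are the same. With the same standardized inputs, power equals that at 8 weeks: 29.6% pairwise, or 87.8% if 0.30 is f. If attrition were 20% (assumption), these become about 27% and 83.3%. If half the effect remained (assumption), they become about 11% and 32%.
- *8 to 12 weeks.* The document gives no effect size, SD or R-squared for this interval, so there is nothing to check the claim against.

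**The case against.** The strongest reply is about scope. The sentence closes the paragraph on the main-effect models, and moderation comes only in the next paragraph, labelled exploratory. The authors may have meant only the 8-week, 12-week and 8-to-12-week comparisons. That reading is possible and limits the weight of the point. But the sentence says all, and the next paragraph uses the same term for the interaction models, so the text does not exclude them.

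A second reply is that a calculation in f units can be applied to an interaction: an interaction with f = 0.30 would also have about 88% power. This is true only because the effect is redefined. At a 50:50 split, f = 0.30 for the interaction means that the arm-specific subgroup differences have an SD of 0.30/sqrt(0.25) = 0.60. If one arm alone departs from the other two, that is a contrast of 0.60/(sqrt(2)/3) = 1.27 SD. This agrees with the table and is far from 0.30 SD.

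Two stronger readings are tempting, and the document supports neither:

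- *That the 12-week and 8-to-12-week models are shown to have less power than the 8-week model.* A shortfall at 12 weeks needs more attrition or a smaller effect than the document gives, and the 10% may already mean loss by the last visit. For 8 to 12 weeks, carrying over the inputs is unsupported but not shown to be false.
- *That equal efficacy across languages is a central aim at risk.* The fourth aim is to develop and deliver a Spanish version, with preliminary efficacy only. Nothing says that a null interaction will be taken as equal effect.

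The 1/p formula also applies only to binary moderators. Baseline severity and engagement may be analysed as continuous.

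**Conclusion.** The scope sentence is too broad, and for the interaction models it is wrong. At the stated 0.30 SD, R-squared 0.20 and 36 evaluable per arm, their power is about 7% to 11%, and the smallest interaction detectable with 80% power is about 1.2 SD. This rests on two-sided testing, binary moderators and assumed splits of 10% to 50%. Even the readings more favourable to the plan in the working leave interaction power far below 80%.

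For 12 weeks the sentence holds only conditionally, and for 8 to 12 weeks it has no stated basis. Because the moderation and 8-to-12-week analyses are labelled exploratory, this is an overstated claim to be reworded, not a flaw in the primary analysis.

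The larger arithmetic problem lies in Sample Size Calculation, where a pairwise 0.30 SD contrast has about 30% power. It is a separate matter: correcting that figure would still leave the scope sentence wrong for interactions.

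**What to change.** Replace the scope sentence in the Statistical Analysis Plan section with:

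> The power calculation (once the 0.30 SD/80% figure in the sample size section is corrected) applies to the between-arm comparisons at 8 weeks, and to those at 12 weeks only under the same standardized effect, R-squared and attrition. The 8-to-12-week and interaction models are exploratory and not powered; they are reported as estimates with 95% CIs, and a non-significant interaction will not be read as equal effect across subgroups.

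The words in brackets are a drafting condition. They should drop out once Sample Size Calculation states what 0.30 refers to and the power that follows from it.

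The cost is small: the wording changes, but no data collection or analysis model does. The article reports 63 of 120 participants enrolled as of April 2026, with analysis to start only after follow-up is complete, so the change can still be made beforehand. The downside is that the stated sensitivity of these analyses becomes less favourable.
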